**Fig. 1 Fig1:**
[figure not shown]
ReduRisk-program

#### Control group

Study participants in the control group will receive the usual care.

#### Test of practicability and quality maintenance

Prior to the start of the study, a first draft of the study information was presented, along with consent forms, program contents, study materials and the tablet-based care plan to pilot-patients. These were optimized according to patient feedback. Additionally, the practicability of the multicomponent interventions and the study procedures were tested and optimized prior to the start of the intervention period. At the start of data collection, study staff and staff in participating departments were trained on the study contents and procedures. The inpatient and post-discharge contacts were quality-assured through manuals, checklists and conversation guidelines.

#### Criteria for modification and discontinuation

If adverse events occur or new needs arise during the intervention phase, these will be documented and the intervention adjusted if necessary. The criteria for dropout are: (1) the participants or legal representatives withdraw informed consent, (2) death of the participant, (3) lack of availability, (4) moving out of the catchment area of the University of Freiburg Medical Center (more than 100 km away), (5) the patient is not yet sufficiently familiar with the ReduRisk-program and has been transferred to a department that does not belong to an intervention cluster.

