#### Blinding

Due to the intervention and randomization design, it will not be possible to blind the study participants and the interventionists, who are responsible for recruiting and carrying out the intervention, or to assign them to the intervention arm in a hidden manner. In order to prevent any influence on the assessment, blinded and trained assessors will carry out the assessment survey both in the intervention and control groups. Study participants and interventionists are required not to reveal the allocation status. Due to pseudonymization, the outcomes will be analyzed without knowledge of the study arm allocation, apart from the process evaluation.

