### Statistical analyses

The superiority of the intervention group over the control group with regards to the two primary endpoints, mobility and ADL function, will be tested as the hypothesis. Medium effect sizes are expected to be in keeping with Martínez-Velilla et al. [70] (Assuming Cohen's d = 0.50). For the alpha level, a Bonferroni adjustment (5% / 2 = 2.5%) has been applied due to multiple testing with two primary endpoints. The achievable number of cases has been taken as *N* = 17 per cluster, with an assumed dropout at t1 of 10% and again 10% at t2. Conservatively, this leaves *N* = 13 cases per cluster with complete data.

Due to clustering by department, calculation of the design effect is required. For the intra-cluster correlation, a value of 0.01 has been assumed, in keeping with Adams et al. [80]. For stepped-wedge designs, power analysis is complex because, in addition to the cluster structure, the temporal effect due to the delayed start of intervention of the clusters will have to be taken into account. However, it is difficult to formulate assumptions about this temporal effect. Since we can assume a medium intra-cluster correlation, the power of the stepped-wedge design is comparable to the power of an ordinary parallel cluster randomized trial [81]. The resulting test power for testing of mean differences under the above conditions with regards to effect size, alpha level and intra-cluster correlation, has been calculated using the program nQuery. The calculation also takes into account that this is an incomplete design, since one of the clusters will be present in the intervention phase from the beginning. A total of six clusters with *N* = 13 per cluster has been assumed. This results in a test power of 94.8% (for a single endpoint), so that the power is above 80% even when multiple testing with two endpoints is taken into account.

Data will be analyzed using IBM SPSS Statistics for windows [82], MPlus [83] and Stata [84]. The content-analytical evaluation of the audio recording of the transcribed focus groups will be based on the procedure of Mayring [85].

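### Dropout criterion 5 can remove intervention patients after allocation on an undefined, exposure-dependent ground with no control-arm counterpart; the direction and size of any bias are unknown

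*Protocol article*

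**What the plan says.** All references are to the protocol article.

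- **Criteria for modification and discontinuation.** The list opens: "The criteria for dropout are: (1) the participants or legal representatives withdraw informed consent, (2) death of the participant". Unavailability and moving away follow. The fifth entry is that the patient is "not yet sufficiently familiar with the ReduRisk-program and has been transferred to a department that does not belong to an intervention cluster". Nothing there limits it to ending the programme while follow-up continues.
- **Control group.** "Study participants in the control group will receive the usual care".
- **Primary hypothesis.** The primary comparison is at discharge (t1).
- **Assessment for evaluation.** Blinded assessors are to see every participant at t0, t1 and t2.
- **Sample size and power calculation.** 612 patients (357 intervention, 255 control) fall to 550 at t1 and 494 at t2 through dropout.
- **Statistical analyses.** Dropout is taken as 10% at t1 and a further 10% at t2, not split by arm or reason. Power rests on 13 "cases per cluster with complete data".
- **Blinding.** "it will not be possible to blind the study participants and the interventionists, who are responsible for recruiting and carrying out the intervention".

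**The concern.** Both conditions of criterion 5 arise after allocation, and the first depends on how much of the programme the patient has absorbed. A control patient has no programme to absorb, and no matching rule covers a control patient who changes department. A transfer during the stay comes before the discharge assessment, so the rule can act before either primary endpoint (SPPB, Barthel Index) is measured.

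A patient who has died or withdrawn consent cannot be followed. A patient meeting criterion 5 may be alive, consenting and still in the same hospital. The rule itself creates that loss. If the t1 and t2 assessments are not made, no later choice of analysis population can recover them. Blinded assessors and pseudonymised analysis do not help, because the selection happens before the assessment.

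At stake is the comparison by randomised department condition on both primary endpoints.

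**Working it through.** **1. Does the rule act on one arm?** By its evident purpose it does: only intervention patients have a programme to become familiar with. Read literally, a control patient moved to another control department also meets both conditions, which can hardly be intended. The wording needs correction on either reading.

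**2. Are these patients lost to assessment?** The dropout arithmetic suggests so:
- t1: 612 × 0.90 = 550.8 (stated 550)
- t2: 612 × 0.90 × 0.90 = 495.7 (stated 494)
- per cluster: 17 × 0.81 = 13.8 (13 used)

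The plan counts dropouts as missing at t1 and t2, whereas Assessment for evaluation has every participant assessed. The two do not fit for a criterion-5 patient who is still reachable.

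**3. Does the rule depend on calendar time?** The design figure is not shown, so the layout is inferred. 357 = 17 × 21 and 255 = 17 × 15, with 21 = 1 + 2 + 3 + 4 + 5 + 6. Together with the statement that one cluster starts in the intervention, this implies six departments over six quarters, with q departments in the intervention in quarter q. The participating departments to which a transfer could trigger criterion 5 then number 6 − q: five in quarter 1, none in quarter 6. Departments outside the trial can trigger it throughout. The chance of removal therefore varies with time, which a stepped-wedge analysis has to separate from treatment.

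**4. Standard error, checked against the stated power.** Hussey-Hughes variance with I = 6 clusters, T = 6 periods, m = 13 per cluster-period, ICC 0.01 and total variance 1:
- s² = 0.99/13 = 0.07615; τ² = 0.01; U = 21; W = V = 91
- numerator: I·s²·(s² + T·τ²) = 6 × 0.07615 × 0.13615 = 0.06221
- denominator: (IU − W)·s² + (U² + ITU − TW − IV)·τ² = 35 × 0.07615 + 105 × 0.01 = 3.7154
- variance = 0.06221/3.7154 = 0.01674; SE = 0.129
- power at d = 0.50, two-sided α = 0.025 (critical value 2.2414): Φ(0.50/0.1294 − 2.2414) = 94.77%

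The article states 94.8%, so the layout and SE are consistent with it. The SE itself is derived, not stated there.

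**5. Size of a possible bias.** If a share f of the intervention arm is removed, and those removed are δ SD worse than those kept, the full-arm mean is the retained mean minus f × δ. The bias in favour of the programme is therefore f × δ, taking f as equal across intervention cluster-periods for simplicity. Two-sided type I error = 1 − Φ(2.2414 − fδ/SE) + Φ(−2.2414 − fδ/SE). Both f and δ are assumptions.

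| f (patients of 357) | δ = 0.25 | δ = 0.5 | δ = 1.0 |
|---|---|---|---|
| 2% (7) | 0.005 SD; 2.5% | 0.010 SD; 2.5% | 0.020 SD; 2.7% |
| 5% (18) | 0.0125 SD; 2.6% | 0.025 SD; 2.8% | 0.050 SD; 3.6% |
| 10% (36) | 0.025 SD; 2.8% | 0.050 SD; 3.6% | 0.100 SD; 7.2% |

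Each cell gives the bias, then the type I error against a nominal 2.5%. As a share of d = 0.50 the bias runs from 1% to 20%. With δ = 0 it is zero; with δ negative it works against the programme.

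**The case against.** The article defines no primary analysis population and nowhere says that criterion-5 patients are left out of it. The section heading concerns modification and discontinuation, and its opening sentence is about adjusting the intervention. The 13 complete cases are a cautious cell size for power, not an analysis rule. Analysis populations and missing-data handling commonly belong to a statistical analysis plan, which is not shown. This stands in part: exclusion from the primary analysis is an inference from the dropout wording and arithmetic. It does not dispose of the point, because a stated rule that ends data collection cannot be repaired in an analysis plan.

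A reader might go further and infer that unblinded staff remove sicker patients and so flatter the programme. The documents do not support that:
- No section says that transferred patients have worse function; a transfer can follow recovery as well as deterioration. The Background notes that projects to close the technology gap have had trouble reaching vulnerable people, but that does not concern transferred patients.
- No judge of familiarity is named. The unblinded interventionists are the likely ones, since they teach and supervise the modules, but that too is an inference.

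The size can also be disputed. The rule is narrow, needing both insufficient familiarity and a particular kind of transfer. The 10% row uses the entire t1 dropout allowance and leaves nothing for death, withdrawal or unavailability. At 2% the effect on type I error is negligible. These objections stand, and the upper end of the table is an outer bound under assumption, not an expectation.

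**Conclusion.** The point holds as a defect in a stated rule. Criterion 5 permits post-allocation dropout on an undefined ground tied to intervention exposure. It has no control-arm counterpart, can operate before the discharge comparison, and conflicts with assessing all participants at every time point. That it acts on one arm follows from its purpose, that it varies by quarter from an inferred layout, and that it reaches the primary analysis from the dropout arithmetic.

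The direction and size of the bias are unknown. The range of 0.005-0.10 SD, with type I error of about 2.5-7.2%, rests on assumed values of f and δ and on a derived SE of 0.129. A claim that the rule most likely favours the programme goes beyond the documents. The case for change does not rest on the size: the loss is avoidable and, once it has happened, may not be recoverable.

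**What to change.** - Remove criterion 5 from the dropout criteria. For the evaluation, treat such a transfer as incomplete exposure to the programme only. Whether programme delivery continues after a transfer is a separate matter on which this point takes no position.
- Assess these patients at t1 and t2 like everyone else, as Assessment for evaluation already provides.
- Analyse them under the allocated condition of the admitting department in the quarter of enrolment.
- Report transfers between departments by arm. Any analysis that leaves transferred patients out should be a sensitivity analysis only.

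The cost is a change of protocol wording and a few more assessments. The estimate may be slightly diluted by under-exposed patients. The planned power of 94.8% is not reduced by keeping them in the count, apart from any such dilution.

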### Outcome measures and assessments

#### Primary and secondary outcomes

The following primary outcome measures are the patient-related endpoints:Mobility, assessed by SPPB [75],Activities of daily living, assessed by Barthel Index [76].The following secondary outcome measures are the patient-related endpoints:Delirium, assessed by 3D-CAM (at t2 by retrospective survey) [65],Cognition, assessed by Montreal Cognitive Assessment (MOCA) [77],Falls, assessed by number and injuries / fractures,Grip strength, assessed by dynamometer,Health-related quality of life, assessed by SF-12 [78],Potentially Inappropriate Medications (PIM), assessed by STOP / START criteria, version 2 [73].Health economics: health care costs and re-hospitalization from AOK claims data (Allgemeine Ortskrankenkasse).

#### Assessment for evaluation

Blinded and trained assessors will evaluate all study participants at three consecutive time points: at admission (t0), discharge (t1) and at six months post-discharge (t2). For the health economic evaluation (t3), costs and re-hospitalizations will be assessed based on claims data from the statutory health insurance organization the AOK. The measurement concept including measurement time points and assessment instruments used to measure primary and secondary outcomes is shown in Table 1 “Assessment and time of measurement”.

**Table 1 Tab1:** Assessments and time of measurement

Month	0	At discharge	6	18
**Time of measurement**	**t0**	**t1**	**t2**	**t3**
**Risk-Screening**				
Functional decline and re-hospitalization (ISAR)	X			
Falls/ Immobility (SPPB)	X			
Delirium (risk-screening according to UKF-delirium standard, 3D-CAM)	X			
**Basic Data**				
Sociodemographic data	X			
Diagnoses	X			
**Primary Outcome**				
Mobility (SPPB)	X	X	X	
Activities of daily living (Barthel index)	X	X	X	
**Secondary Outcome**				
Cognition (MOCA)	X	X	X	
Delirium (3D-CAM)	X	X	X	
Falls (Number in total, injuries / fractures)	X	X	X	
Grip strength (Dynamometer)	X	X	X	
Health-related quality of life (SF-12)	X	X	X	
Potentially inappropriate medications (STOPP/START)	X	X	X	
Re-hospitalization (AOK—claims data)		→		X
Health care costs (AOK—claims data)	→			X

*3D-CAM *Confusion Assessment Method, *AOK *Allgemeine Ortskrankenkasse (Statutory Health Insurance), *ISAR *Identification of Seniors At Risk, *MOCA *Montreal Cognitive Assessment, *SPPB *Short Physical Performance Battery, *STOPP/START *Screening Tool of Older Persons’s Prescriptions / Screening Tool to Alert to Right Treatment, *UKF-Delirium Standard *Internal Standard for Delirium Prevention and Treatment of the University of Freiburg Medical Center

#### Sample size and power calculation

We aim to recruit 612 patients to the study, with 357 patients in the intervention group and 255 in the control group. Assuming a dropout rate of 20%, the number of study participants in the intervention and control group should correspond to *N* = 550 at t1 and *N* = 494 at t2. For the health economic evaluation, the number of cases *N* = 247 will be assumed, as approximately 50% of all participants are AOK patients. The planned patient flow is shown in Fig. 2 “Trial design”.

**Fig. 2 Fig2:**
[figure not shown]
Trial design

#### Process evaluation

Contextual factors are essential for the evaluation and sustainable implementation of complex interventions [79]. For this purpose, we will assess (1) contextual factors at the patient level (sociodemographic background, diagnoses) through assessment of routine clinical data, (2) patient adherence to the intervention through structured interviews during the inpatient and post-discharge phases and surveys of tablet device use and (3) adherence of the interventionists to the manual through the documentation of the accomplished interventions. Additionally, we will address the following topics at the organizational level through seven semi-structured, 45-min focus group interviews with study staff and study-involved staff from the six departments: a) Feasibility of the intervention modules, b) Obstacles and factors conducive to implementation in accordance with the manual, c) Perceived acceptance of the study participants, d) Benefit and suggestions for optimization.

#### Recruitment of participants

Interventionists will compile a daily list of newly admitted patients aged 70 and over hospitalized at one of the six participating departments of the University of Freiburg Medical Center. Patient records will be checked for the presence of inclusion criteria. The interventionists will then introduce the ReduRisk-project to potentially eligible patients through the use of comprehensive study information, and informed written consent from those interested in participating. If patients are incapable of giving consent due to severe cognitive impairment, informed written consent for study participation can be obtained from the legal guardian. In this case, a proxy assessment will be conducted with the legal guardian or with the relatives of the person concerned. If patients subsequently show an increased risk of functional impairment, immobility, falls, delirium or re-hospitalization during risk-screening, they can still participate in the study.

#### Assignment and randomization

ReduRisk is a monocentric stepped-wedge study with quarterly, computer-generated, cluster randomization of six departments to intervention and control groups (1 hospital department = 1 cluster). The study center will carry out allocation assignments independently of ward staff and their respective interventionists.

#### Blinding

Due to the intervention and randomization design, it will not be possible to blind the study participants and the interventionists, who are responsible for recruiting and carrying out the intervention, or to assign them to the intervention arm in a hidden manner. In order to prevent any influence on the assessment, blinded and trained assessors will carry out the assessment survey both in the intervention and control groups. Study participants and interventionists are required not to reveal the allocation status. Due to pseudonymization, the outcomes will be analyzed without knowledge of the study arm allocation, apart from the process evaluation.

### Statistical analyses

The superiority of the intervention group over the control group with regards to the two primary endpoints, mobility and ADL function, will be tested as the hypothesis. Medium effect sizes are expected to be in keeping with Martínez-Velilla et al. [70] (Assuming Cohen's d = 0.50). For the alpha level, a Bonferroni adjustment (5% / 2 = 2.5%) has been applied due to multiple testing with two primary endpoints. The achievable number of cases has been taken as *N* = 17 per cluster, with an assumed dropout at t1 of 10% and again 10% at t2. Conservatively, this leaves *N* = 13 cases per cluster with complete data.

Due to clustering by department, calculation of the design effect is required. For the intra-cluster correlation, a value of 0.01 has been assumed, in keeping with Adams et al. [80]. For stepped-wedge designs, power analysis is complex because, in addition to the cluster structure, the temporal effect due to the delayed start of intervention of the clusters will have to be taken into account. However, it is difficult to formulate assumptions about this temporal effect. Since we can assume a medium intra-cluster correlation, the power of the stepped-wedge design is comparable to the power of an ordinary parallel cluster randomized trial [81]. The resulting test power for testing of mean differences under the above conditions with regards to effect size, alpha level and intra-cluster correlation, has been calculated using the program nQuery. The calculation also takes into account that this is an incomplete design, since one of the clusters will be present in the intervention phase from the beginning. A total of six clusters with *N* = 13 per cluster has been assumed. This results in a test power of 94.8% (for a single endpoint), so that the power is above 80% even when multiple testing with two endpoints is taken into account.

Data will be analyzed using IBM SPSS Statistics for windows [82], MPlus [83] and Stata [84]. The content-analytical evaluation of the audio recording of the transcribed focus groups will be based on the procedure of Mayring [85].

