#### Primary hypothesis

Our primary hypothesis is that the ReduRisk-program will significantly reduce immobility and decline in activities of daily living, compared to usual care at discharge.

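### Holm's procedure could replace the fixed 2.5% Bonferroni level for the two primary endpoints: same 5% familywise error, slightly more power for the second endpoint

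*Protocol article*

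**What the plan says.** There are two primary endpoints, mobility by SPPB and activities of daily living by Barthel Index (Primary and secondary outcomes). The primary hypothesis concerns discharge: the program will "significantly reduce immobility and decline in activities of daily living, compared to usual care at discharge".

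The Statistical analyses section describes the test: "The superiority of the intervention group over the control group with regards to the two primary endpoints, mobility and ADL function, will be tested". On multiplicity it says that "a Bonferroni adjustment (5% / 2 = 2.5%) has been applied due to multiple testing with two primary endpoints". It gives a power of 94.8% for one endpoint and adds that power stays above 80% once both are taken into account. No step-down procedure is mentioned. No sentence says in so many words whether success needs both endpoints or only one.

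**The concern.** A fixed 2.5% for each endpoint holds the familywise error at 5% but leaves something unused. Once one endpoint is significant at 2.5%, the other can be tested at the full 5% without raising the familywise error. That is Holm's rule for two hypotheses. A result with p = 0.01 on SPPB and p = 0.04 on Barthel, for example, supports one claim under Bonferroni and two under Holm.

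What is at stake is the second endpoint only. The program is meant to act on both mobility and daily function, so the chance of establishing both matters to the trial, and part of it is given up for no gain in error control.

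**Working it through.** **Inputs from the protocol article**
- Effect size: "Assuming Cohen's d = 0.50".
- Clustering: "For the intra-cluster correlation, a value of 0.01 has been assumed".
- Cases: "A total of six clusters with *N* = 13 per cluster has been assumed".
- Allocation: "with 357 patients in the intervention group and 255 in the control group". With 17 recruited per cell, 357/17 = 21 and 255/17 = 15. That is a grid of 6 departments by 6 quarters with one department in intervention from the start (1+2+…+6 = 21 intervention cells).
- Dropout: 10% by discharge and 10% again by six months.

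**Assumptions, because the article does not give them**
- Tests are two-sided.
- The 13 cases are per department and quarter. The stated power is not reached with 13 per department in total: a parallel trial of 3 + 3 clusters of 13 gives 43.8%.
- The correlation between the two test statistics is unknown and is varied from 0 to 0.7.

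**Step 1: reproduce the plan's figure.** The Hussey–Hughes stepped-wedge variance (fixed period effects, random department effect, total SD 1), with 13 per cell and ICC 0.01, gives SE = 0.1294.
- Power at two-sided 2.5% = Φ(0.50/0.1294 − 2.241) = Φ(1.623) = 94.8%, as stated.
- Power at two-sided 5% = Φ(0.50/0.1294 − 1.960) = Φ(1.904) = 97.15%.

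So the Bonferroni level is already inside the 94.8%.

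**Step 2: power to show both endpoints, correlation 0.**
- Bonferroni: 0.9477² = 0.898.
- Holm needs both significant at 5% and at least one at 2.5%: 0.9715² − (0.9715 − 0.9477)² = 0.9438 − 0.0006 = 0.943.

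**Step 3: range over the correlation.** The values below come from the bivariate normal distribution of the two test statistics.

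| Cases per cell | Correlation | Both, Bonferroni | Both, Holm | Gain (points) |
|---|---|---|---|---|
| 13 | 0 | 89.8% | 94.3% | 4.5 |
| 13 | 0.7 | 91.6% | 95.0% | 3.4 |
| 15 | 0 | 93.8% | 96.8% | 3.0 |
| 15 | 0.7 | 94.8% | 97.1% | 2.3 |

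The rows with 15 per cell reflect the primary time point: 17 × 0.9 = 15.3 at discharge. The 13 also allows for dropout to six months (17 × 0.9 × 0.9 = 13.8, taken as 13).

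**Step 4: what does not change.** With 13 per cell, power to show at least one endpoint is the same under both rules: 99.7% at correlation 0 and 97.9% at 0.7. With both null hypotheses true, the familywise error is also the same (4.9% at correlation 0, 4.3% at 0.7). With one null true and the other endpoint at d = 0.50, Holm falsely rejects the null endpoint in 4.9% (correlation 0) or 4.7% (correlation 0.5) of trials, within the 5% limit.

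**The case against.** The strongest reply is that nothing here is wrong. Bonferroni controls the error, the power statements are correct, and a choice between two valid procedures is partly preference. The 2.5% also stands among the inputs to the power calculation, and a statistical analysis plan that is not shown could still specify a step-down test. All of that stands. It limits the point to a suggestion, but Holm remains at least as powerful at the same error rate.

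The gain also depends on the inputs. SPPB and Barthel both measure physical function, so independence, which gives the largest gain, is unlikely. At discharge the larger cell size shrinks the gain further. Both objections are right, and the table shows their effect. Larger gains appear with a smaller effect or a higher ICC, but those are not the plan's inputs and cannot carry the point.

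A reader might go further and infer from the word joining mobility and daily living in the primary hypothesis that both endpoints must be significant, so that no split is needed and each may be tested at an unadjusted 5%. The article does not support this. The Secondary hypothesis section joins its outcomes in the same list style, where an all-must-succeed rule would not be inferred. The Statistical analyses section speaks of multiple testing and of power for one endpoint, which points to separate claims. Testing each at 5% would apply only if the sponsor defined success as both being significant, and it would remove the option of claiming one endpoint alone.

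**Conclusion.** The point holds as a minor efficiency improvement. The fixed 2.5% is valid and the planned power is adequate, so a reader should not conclude that the trial has an inflated error rate, a wrong power statement or too few patients on this account.

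Under the plan's d = 0.50 and ICC 0.01, Holm adds about 3.4 to 4.5 points to the power to show both endpoints with 13 per cell, and about 2 to 3 points with 15 per cell. It adds nothing to the chance of showing at least one. These sizes rest on two-sided tests, the per-cell reading of the case numbers, equal effects on both endpoints and an endpoint correlation between 0 and 0.7.

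**What to change.** State that SPPB and Barthel Index at discharge are separate primary claims and that Holm's procedure will be used at analysis: the smaller p-value is tested at 2.5% and, if it is significant, the other at 5%. Keep the sample size calculation at 2.5%, which remains a safe basis. Fix the rule before any results by group are seen.

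The cost is one sentence and no extra patients. The drawback is that confidence intervals matching Holm are less simple than Bonferroni intervals, so the plan should also say which intervals will be reported.

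### The 94.8% power figure matches only a normal reference, which runs at about 3.5% rather than 2.5% with six departments; at the stated 13 patients per department-quarter, a small-sample t test has about 92%

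*Protocol article*

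**What the plan says.** Under Assignment and randomization, the unit is the department: "cluster randomization of six departments to intervention and control groups (1 hospital department = 1 cluster".

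Under Statistical analyses, the power inputs are:

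- a medium effect ("Assuming Cohen's d = 0.50");
- a split significance level ("a Bonferroni adjustment (5% / 2 = 2.5%) has been applied due to multiple testing with two primary endpoints");
- a correlation within departments ("For the intra-cluster correlation, a value of 0.01 has been assumed");
- a sample for analysis ("A total of six clusters with *N* = 13 per cluster has been assumed").

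The power "has been calculated using the program nQuery", and the outcome is "This results in a test power of 94.8% (for a single endpoint". From this the article concludes that power stays above 80% when both endpoints are considered. It names no reference distribution, degrees of freedom or small-sample correction for the power figure, and no test for the primary analysis.

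**The concern.** A normal reference is safe when the variance of the treatment estimate is known or estimated from many clusters. Here the between-department variance comes from six departments. If the power was computed as though that variance were known, the figure describes a test that rejects too often under the null. It is then not the power of a test run at the 2.5% that the Bonferroni split promises.

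Two things are at stake: an accurate power statement, and the error rate of the two primary tests should the same reference be carried into the analysis. The number of departments is fixed, so the small-cluster problem has to be handled through the choice of test.

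**Working it through.** **Inputs.** From Statistical analyses: d = 0.50 (SD 1), 2.5% per endpoint, intra-cluster correlation 0.01, six departments, one of them in the intervention phase from the start. Sidedness is not stated; two-sided is taken because it reproduces the figure.

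The layout follows from the recruitment numbers under Sample size and power calculation. At 17 per department-quarter, 357/17 = 21 intervention cells and 255/17 = 15 control cells, so 36 cells in a 6 × 6 wedge (1 + 2 + … + 6 = 21). The 13 therefore counts patients per department-quarter: 17 × 0.9 × 0.9 = 13.77, taken down to 13.

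**Step 1: reproduce 94.8%.** The Hussey-Hughes variance (random department intercept, fixed quarter effects) is

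Var = Iσ²(σ² + Tτ²) / [(IU − W)σ² + (U² + ITU − TW − IV)τ²]

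with I = T = 6, U = 21 treated cells, W = V = 91 (sums of squared column and row totals), τ² = 0.01 and σ² = 0.99/13 = 0.07615.

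- Numerator: 6 × 0.07615 × (0.07615 + 0.06) = 0.06221
- Denominator: 35 × 0.07615 + 105 × 0.01 = 3.715
- Var = 0.01674, SE = 0.1294, d/SE = 3.864
- Normal-reference power: Φ(3.864 − 2.241) = 94.77%

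This matches. Other readings do not: one-sided 2.5% gives 97.2%, a 6 × 7 wedge 95.2%, a parallel cluster design 96.1 to 96.6%, and t with 24 df 92.2%. A t reference with several hundred df gives 94.65%. That is close, but it also ignores the small number of departments.

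**Step 2: t reference at the same inputs.** Degrees of freedom: 36 cells − 6 departments − 5 quarters − 1 treatment = 24. The two-sided 2.5% critical value is 2.391. With noncentrality 3.864 the power is 92.2%.

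**Step 3: level and power with estimated variances.** The same design was simulated at n = 13 and correlation 0.01 (40,000 runs; 3,000 to 8,000 for permutation).

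| Test | Type I error | Power |
|---|---|---|
| REML, normal reference | 3.5% | 94.6% |
| REML, t with 24 df | 2.5% | 92.9% |
| REML, Satterthwaite | 2.5% | 93.3% |
| REML, Kenward-Roger | 1.4% | 90.2% |
| Permutation over 720 department orders | 2.1 to 2.8% | 86 to 90%, by statistic |

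With the true variances plugged in, the normal reference has a level of 2.4%, so the excess comes from estimating them. With ML instead of REML it rises to 4.1%. At correlation 0 the REML normal test is at 2.5%, so the excess disappears. At correlation 0.05 (an assumption, not in the article) it is 3.9%.

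Estimators that use only within-department information also hold the level but give up power: departments as fixed effects reach 80.1% (level 2.6%), and a within-department permutation statistic 74%. They are outside the ranges in the table.

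**Step 4: the sample expected at discharge.** Primary hypothesis places the primary comparison at discharge. Sample size and power calculation expects 550 patients then, so 550/36 = 15.28 per cell and σ² = 0.99/15.28 = 0.0648.

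- Var = 6 × 0.0648 × 0.1248 / (35 × 0.0648 + 1.05) = 0.01462; SE = 0.1209; d/SE = 4.135
- t with 24 df: 95.3%
- Normal reference, for comparison: Φ(4.135 − 2.241) = 97.1%

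**The case against.** The strongest reply is that the figure carries its own margin. The 13 allows for dropout at both discharge and six months, while the primary comparison is at discharge, where about 15 per department-quarter are expected. There a t test with 24 df has 95.3%. This stands. A reader might infer that 94.8% is too high for any test that keeps 2.5%; the article's own discharge numbers contradict that. What remains is that the figure is stated for 13, and at 13 it belongs to a test that exceeds its level.

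A second reply is that a planning approximation does not bind the analysis. This also stands. A reader might infer that the trial will analyse with a z or Wald test and spend up to about 7% over two endpoints. The article names no such test, an SAP may specify a small-sample method, and 7% is only the additive ceiling of 2 × 3.5%. Leaving the analysis method to the SAP is no fault.

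A third reply is that nothing changes in the conclusion, which is right for one endpoint under the tests tabulated. A reader might go on to say that the trial is underpowered for success on both endpoints. The Bonferroni split does not require both to succeed. Even if it did, 0.922² = 85% with the t test, assuming independent endpoints; only the weaker permutation statistics would fall short (0.86² = 74%, 0.90² = 81%). Larger inflation under correlation that decays over time rests on inputs the article does not give.

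**Conclusion.** The point holds as a minor one. At its stated inputs, 94.8% is a normal-reference figure, and that reference has a true level of about 3.5% with six departments. A t test that holds 2.5% has 92 to 93% power at 13 per department-quarter, a loss of roughly 2 to 3 points; a permutation test loses roughly 5 to 9.

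This rests on three things: the reference being inferred from the numerical match, a two-sided 2.5% test, and a department effect that is constant over time with correlation 0.01. The excess over the nominal level is about one percentage point and vanishes at correlation 0. Single-endpoint power above 80% is not in question for the tests recommended here.

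**What to change.** Under Statistical analyses, restate single-endpoint power as about 92% at 13 patients per department-quarter, two-sided 2.5%, with a t reference on 24 degrees of freedom. Add that the same test has about 95% at the roughly 15 per department-quarter expected at discharge.

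State that both primary tests use a small-sample reference (Satterthwaite or Kenward-Roger t, or a permutation test over the 720 department orders), unless the SAP already says so. If permutation is chosen, name the statistic and quote power for it, because 86 to 90% depends on that choice. In choosing between the t methods, note that Satterthwaite held 2.5% at correlation 0.01 but reached 3.3% at an assumed 0.05, where Kenward-Roger was at 2.3%.

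The cost is a sentence or two and a slightly lower power figure. No extra patients are needed and the design does not change.
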